##### Cognitive performance

The *Montreal Cognitive Assessment* (MoCA) [44] is a brief screening tool of global cognition to reveal mild cognitive impairment and an early stage of Alzheimer’s disease. It assesses several cognitive domains, like short-term memory recall, visuospatial abilities, multiple aspects of executive functions, attention, concentration and working memory, language and orientation to time and place. MoCA scores range between 0 and 30. A score of 26 or above is considered to be normal [44].

##### Psychosocial well-being

The *Center for Epidemiological Studies Depression Scale* (CES-D) [54] is used to screen for depressive symptoms and mood disorders with an eleven-items questionnaire, scoring between zero and three points for each item. It has demonstrated validity for research conducted in elderly populations [55]. Two items regarding the exhaustion of residents (“Everything was effort”; “I could not get going”) will also be used to assess the ‘exhaustion’ for the frailty index.

### Intervention

The exercise program consists of 32 sessions for a period of 16 weeks. One training session has a duration of 45–60 min and takes place twice a week. Exercise sessions will be administered by at least one certified exercise scientist or physiotherapist with group sizes ranging from four to 15 participants. The program follows IAGG guidelines and combines previously published exercises that have proven to be beneficial for cognitive-motor performance in older people in the community and in need of care [7, 8, 12, 20, 35, 56–59]. Training focusses on daily situations which are commonly associated with an increased fall risk and it mostly includes challenging walking exercises (e.g., brisk walking, starting, stopping, avoiding obstacles, turns). During these exercises, participants are also exposed to a variety of cognitive tasks under single- and dual-task conditions, designed to challenge their focus of attention with acoustic and visual stimuli and specific executive functions. Furthermore, exercises for strength, balance and flexibility as well as endurance performance associated with walking are integrated.

To ensure a controllable structure, training sessions are divided in five parts: 1. 5–10 min mobilisation and warm-up (e.g., range of motion exercises for the wrists, hip, shoulders, knees, and ankles). 2. 10 min coordination, balance, and cognitive exercises (e.g., standing balance, bodyweight shifting, motivational cognitive-motor games with group interaction including balls and scarfs). 3. 20 min aerobic walking exercises (e.g., under different single and dual-task conditions). 4. 10 min strength exercises (e.g., chair rises, upper body and trunk exercises with additional materials and weights, functional lower-limb exercises). 5. 5–10 min calm down (e.g., stretching and relaxing exercises).

During the first step of the conceptualization, qualitative guided interviews were conducted with five residents of a nursing home facility. The interviews assessed different domains regarding ADL, need of support, participation in social activities as well as expectations and wishes regarding a training program. Moreover, a feasibility study (currently under review) was conducted to examine the adherence and acceptance of the program. Taking into account these previously inquired desires and preferences of the residents, a focus is set on everyday skills to promote ADL, cognition and psychosocial resources. For example, by using motivational equipment with different colors and music during the exercise sessions, a stimulating environment will be provided to promote participant’s retention. The exercise program will be continuously adapted to the residents’ capacity and hence, it is organized as a progressive challenge to expand participants’ resources in accordance to the F.I.I.T. principle [60]. The intensity of exercises will vary between moderate and vigorous. This will be ensured by adjusting the duration, frequency, difficulty, range of motion and/or intensity of the exercises. For example, endurance exercises, like 15 m walks, will range from ten up to 22 walks within one session. For residents who are unable to walk a program will be conducted with exercises exclusively in a sitting position. Regarding resistance exercises, progression will be ensured by adjusting the number of repetitions (from 5 to 10 to 15 to 20), the number of sets (1, 2 or 3), and/or by usage of additional weights (1 or 2 kg). For executing static, dynamic balance, and coordination exercises the difficulty level will be raised by changing exercise positions (e.g., sitting, standing, feet together, side-by-side, semi-tandem, tandem, standing on one leg). To assess the intensity of training, instructors will use the Borg Scale of Perceived Exertion [61].

Discontinuation of the intervention may occur in case of health decline or if a participant wishes to stop taking part in the group intervention. To improve adherence and to promote retention, the therapists will give explanations about the purpose of the intervention and the possible benefits of the exercises. Attendance of each participant will be recorded and reasons for drop outs will be documented. No other concomitant group exercise interventions are permitted besides usual care and physiotherapy. Control group participants will be asked to continue their regular everyday activities.

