#### Recruitment of nursing homes

Eight cities and their surroundings throughout various regions in Germany (Bremen, Chemnitz, Frankfurt, Hamburg, Karlsruhe, Nuremberg, Paderborn and Stuttgart) will recruit 48 nursing homes in total (six per site). The institutions involved are deliberately selected based on their basic structural figures (number of nursing places, number of employees, urban or rural district, social-economic status), in order to analyze the applicability of the program under a wide range of conditions. Therefore, a list of all nursing homes will be created. It will then be stratified by their structural characteristics and afterwards the nursing homes will be randomly selected. Participation is voluntary and will not be remunerated. In case a requested nursing home declines to participate, another facility with similar characteristics will be requested instead.

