### Data collection, management, and analysis

#### Statistical analysis

We will evaluate the effects of the intervention on every quantitative, qualitative, and ordinal outcome, using repeated measures or mixed models, “t” tests, Kruskall-Wallis Mann-Witney tests or the Chi-square tests, depending on the type of outcome and their normal or non-normal distribution. The primary analysis will be a mixed model between-group comparison of the SPPB, gait variables, Serial Sevens, and Verbal Fluency Test, utilising all available data points during follow-up. We will use the Bonferroni correction to appropriately adjust the overall level of significance for multiple comparisons. Between-group differences for all primary and secondary outcomes will be adjusted for baseline values, age, sex, and education. Secondary outcomes will be analysed with similar methodology, using repeated measures mixed model between-group comparisons. All statistical analyses will be performed using SPSS Statistics for Windows (version 25.0, IBM). Statistical significance level is set at *p* < 0.05.

Intention-to-treat analysis will be performed (participants who are randomized into groups after the collection of baseline data). For the intention-to-treat analysis, data of all trial patients in the groups to which they were randomized will be processed, regardless of whether they received or adhered to the allocated intervention. It is assumed that the majority of participants in the two arms will receive the appropriate number of intervention sessions. In addition, a per-protocol analysis of the participants who completed the study without major protocol violation (e.g., who attended more than 80% of the training sessions), will be performed. The per-protocol analysis will be performed as a secondary analysis, if there is a sufficient number of participants in the two arms, who do not receive the intervention protocol or are lost to outcome assessment. Data from those participants, who do not violate the treatment protocols, will be included in the per-protocol analysis. The multiple imputation (MI) technique will be used for dealing with missing data under the assumption that data are missing at random.

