#### Sample size estimate / power calculations

The required sample size was calculated with G*Power (Version 3.1.9.2, Heinrich Heine University of Duesseldorf) [62]. The sample size calculation was approximated with a 2 × 3-factorial analysis of variance (ANOVA) for repeated measures (within-between interaction, small effect size, power of .80 [1-β], 2-sided α-error (95% CI), 2 groups, 3 measurements) based on the primary outcome Short Physical Performance Battery (SPPB). The small effect size used for the calculation of required sample size is based on literature reviews and assumptions of clinically relevant changes for residents in nursing homes with probable cognitive impairment [63]. One hundred eight individuals per region are required in order to detect a clinically meaningful change of ≥1.0 point with a SD of 0.99 points. To account for potential dropouts before study completion, we will inflate the sample size by 30% (20% losses during follow-up; 10% mortality), resulting in a total sample size of 1120 individuals (140 per centre with 70 participants allocated to each group).

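### The intervention arm trains in groups, but neither the sample size nor the stated adjustment allows for correlation within a training group

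*Protocol article*

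**What the plan says.** All places are in the protocol article.

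- **Assignment of interventions:** individual residents are allocated by lot, stratified on sex, age and MoCA score.
- **Recruitment of nursing homes:** the eight regions "will recruit 48 nursing homes in total (six per site").
- **Intervention:** "Exercise sessions will be administered by at least one certified exercise scientist or physiotherapist with group sizes ranging from four to 15 participants". Group interaction is part of the content. The control arm carries on with everyday activities until its waiting time ends.
- **Sample size estimate / power calculations:** "The sample size calculation was approximated with a 2 × 3-factorial analysis of variance (ANOVA) for repeated measures", with these settings: "within-between interaction, small effect size, power of .80 [1-β], 2-sided α-error (95% CI), 2 groups, 3 measurements". The result is 108 residents per region, to "detect a clinically meaningful change of ≥1.0 point with a SD of 0.99 points". The only inflation is 30%, for losses to follow-up and deaths, giving 140 per centre and 1120 in total. No ICC or design effect appears.
- **Statistical analysis:** the primary analysis is a mixed model. "Between-group differences for all primary and secondary outcomes will be adjusted for baseline values, age, sex, and education". Exercise group, instructor, home and region are not in that list, and the random effects are not described.

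**The concern.** This is an individually randomised group-treatment trial. Trainees who share sessions, an instructor and a social setting for 16 weeks may end up more alike than trainees in other groups. Controls have no such shared treatment. The extra correlation therefore arises in one arm only, and individual randomisation does not remove it.

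If the analysis carries no term for the training group, the information in the intervention arm is overcounted: the standard error of the treatment effect is too small, the confidence interval too narrow and the type I error above its nominal level. A sample size computed on independent residents likewise overstates the power available at the number it gives.

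**Working it through.** **Inputs from the protocol.** 1120 residents, 70:70 in each of eight centres, so 560 per arm; 48 homes; training groups of 4 to 15; 108 per region at power 0.80; 30% inflation; significance level 0.05, two-sided.

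**Assumptions (not in the protocol).** A group ICC of 0.01 to 0.10 in the intervention arm; one training group per home; equal outcome variance in the two arms.

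**The plan's own figures.** 108 × 1.3 = 140.4, taken as 140, and 140 × 8 = 1120, as stated. The 108 cannot be rebuilt from the stated inputs. Reading the small effect as f = 0.10, a within-person correlation of 0.5 gives 164; 108 needs a correlation of about 0.67, which is not stated. A difference of 1.0 with SD 0.99 needs only 16 per arm in a two-sample comparison. None of these routes contains a clustering term. I therefore take 0.80 at 108 as given and ask what group correlation does to it.

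**Group size m.** 560/48 = 11.7 as randomised; 560 × 0.7/48 = 8.2 after 30% loss.

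**Formulas.**
- Variance factor in the trained arm: D = 1 + (m − 1) × ICC. In the control arm it is 1.
- Variance factor for the difference: A = (1 + D)/2. The true standard error is √A times the naive one.
- Type I error of the naive test: 2[1 − Φ(1.96/√A)].
- Power with the correct standard error: Φ(2.80/√A − 1.96), where 2.80 = 1.96 + 0.84.
- Number per region that restores 0.80: 108 × A.

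**Example.** m = 11.7, ICC 0.05: D = 1.533, A = 1.267, √A = 1.125. Type I error = 2[1 − Φ(1.741)] = 0.082. Power = Φ(0.528) = 0.70.

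| m | ICC | A | Type I error | Power at 108 | n per region |
|---|---|---|---|---|---|
| 8.2 | 0.01 | 1.04 | 5.4% | 0.79 | 112 |
| 8.2 | 0.02 | 1.07 | 5.8% | 0.77 | 116 |
| 8.2 | 0.05 | 1.18 | 7.1% | 0.73 | 128 |
| 8.2 | 0.10 | 1.36 | 9.3% | 0.67 | 147 |
| 11.7 | 0.01 | 1.05 | 5.6% | 0.78 | 114 |
| 11.7 | 0.02 | 1.11 | 6.2% | 0.76 | 120 |
| 11.7 | 0.05 | 1.27 | 8.2% | 0.70 | 137 |
| 11.7 | 0.10 | 1.53 | 11.3% | 0.62 | 166 |

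At the limits of the stated group size, the same formula gives a type I error of 5.2% to 6.8% (groups of 4) and 5.8% to 13.3% (groups of 15).

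**Group versus home.** A simulation used 48 homes with 9 residents per arm in each, randomised within home and analysed without clustering terms. A group effect in the intervention arm only (ICC 0.02, 0.05, 0.10) gave type I error 0.055, 0.078 and 0.095. A home effect common to both arms (ICC 0.05, 0.10) gave 0.043 and 0.037. So omitting group makes the standard error too small, and omitting a shared home effect makes it slightly too large.

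**Whole trial.** Expected completers: 1120 × 0.7 = 784, or 392 per arm. At the worst tabulated factor (A = 1.53), f = 0.10 and a within-person correlation between 0 and 0.67, power for the three-measurement interaction is still about 0.95 or higher. For 1.0 point with SD 0.99, the standard error is 0.99 × √(2 × 1.53/392) = 0.087, so the difference is more than 11 standard errors and power is essentially 1.

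**The case against.** The strongest reply is that the article names a mixed model without listing its random effects. The sentence on adjustment concerns covariates, and a fuller analysis plan could include a group effect. That stands as far as it goes: the analysis is left open, not shown to be wrong. It does not rescue the sample size, which is set out with its method, settings and inflation and has no allowance for clustering.

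A second reply is that every magnitude here rests on an assumed ICC. That also stands. At 0.01 the effect is slight (5.4% error, power 0.79); only the upper part of the range is serious.

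Three stronger readings are tempting, and the document supports none of them:

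- **That the missing home term makes standard errors too small.** Allocation is individual. Where both arms are present in a home, which is implied but not stated, omitting a shared home effect works in the other direction. A home intercept alone would also not repair correlation specific to the training group.
- **That the whole trial is underpowered.** The 0.80 belongs to 108 per region, which is then multiplied over eight regions, and pooled power stays high. A pooled fall to about 0.62 appears only for a standardised difference of 0.2 at a single time point, a calculation the protocol does not make.
- **That drawing lots without home as a stratum would breach the limit of 15 per group.** This needs lots pooled across homes and a single group per home. The protocol states neither, and a home with more trainees could run two groups.

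**Conclusion.** The point holds for the exercise group in the intervention arm. The sample size rests on independent residents, and the stated adjustment has no group term. If the model is fitted with only what is listed, its standard error is too small for any positive group ICC. With about 8 to 12 trainees per group and an assumed ICC of 0.01 to 0.10, the nominal 5% type I error becomes about 5.4% to 11%, and the 0.80 at 108 per region becomes about 0.79 to 0.62.

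The error inflation does not go away with the larger pooled sample, because that sample consists of more groups of the same size. The loss of power is a per-region statement and does not carry over to the trial as a whole at the stated effect. The figures depend on the assumed ICC and on one group per home; smaller groups would reduce them.

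**What to change.** 1. In the primary mixed model, add a random effect for exercise group that acts in the intervention arm only (a partially nested model), with small-sample degrees of freedom. Include home as a design factor. Use the same structure for the secondary outcomes.
2. Record a training-group and instructor identifier for each participant alongside attendance, which is already recorded.
3. Restate the power in the sample size section over an ICC range such as 0.01 to 0.10, and say whether it applies to each region or to the whole trial.

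The cost is a few model terms, slightly wider confidence intervals and a less favourable per-region power. No participants need to be added. The model change should be fixed before analysis.

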### Data collection, management, and analysis

#### Statistical analysis

We will evaluate the effects of the intervention on every quantitative, qualitative, and ordinal outcome, using repeated measures or mixed models, “t” tests, Kruskall-Wallis Mann-Witney tests or the Chi-square tests, depending on the type of outcome and their normal or non-normal distribution. The primary analysis will be a mixed model between-group comparison of the SPPB, gait variables, Serial Sevens, and Verbal Fluency Test, utilising all available data points during follow-up. We will use the Bonferroni correction to appropriately adjust the overall level of significance for multiple comparisons. Between-group differences for all primary and secondary outcomes will be adjusted for baseline values, age, sex, and education. Secondary outcomes will be analysed with similar methodology, using repeated measures mixed model between-group comparisons. All statistical analyses will be performed using SPSS Statistics for Windows (version 25.0, IBM). Statistical significance level is set at *p* < 0.05.

Intention-to-treat analysis will be performed (participants who are randomized into groups after the collection of baseline data). For the intention-to-treat analysis, data of all trial patients in the groups to which they were randomized will be processed, regardless of whether they received or adhered to the allocated intervention. It is assumed that the majority of participants in the two arms will receive the appropriate number of intervention sessions. In addition, a per-protocol analysis of the participants who completed the study without major protocol violation (e.g., who attended more than 80% of the training sessions), will be performed. The per-protocol analysis will be performed as a secondary analysis, if there is a sufficient number of participants in the two arms, who do not receive the intervention protocol or are lost to outcome assessment. Data from those participants, who do not violate the treatment protocols, will be included in the per-protocol analysis. The multiple imputation (MI) technique will be used for dealing with missing data under the assumption that data are missing at random.

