#### Primary outcomes

The following primary outcomes will be measured to evaluate the efficacy of the intervention program:

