##### Dual-task cognitive performance

The *Serial Sevens Test* (SST) [46] aims to assess cognitive functioning. During the SST, participants are being asked to count down from a certain number in steps of seven. Due to the poor cognitive functioning of most participants, a simpler version of the SST will be administered, in which participants have to count down in steps of 3 (S3T) and steps of 1 (S1T). The S3T and S1T will be tested during a single- and dual-task condition (i.e. during gait), in order to evaluate the cost of dual-tasking for cognitive functioning. The number of correct answers within 15 s will be recorded during single- and dual-task conditions as well as the gait parameters step length, step width, gait speed, and double support phase under dual-task conditions with a gait analysis system.

The *Verbal Fluency Test* (VFT) is an additional test for cognitive functioning and part of the MoCA [44]. The VFT is a phonemic fluency test, in which participants are asked to name as many words as possible in a certain time, starting with a specific letter (not allowed are names or numbers). It was shown that verbal fluency is reduced in elderly people with mild cognitive impairments as compared to their non-impaired peers [47]. In accordance to the S3T and S1T, the VFT will be administered during single- and dual-task conditions, to evaluate the cost of dual-tasking for cognitive functioning. The number of correct answers within 15 s will be recorded during single- and dual-task conditions as well as the gait parameters step length, step width, gait speed, and double support phase under dual-task conditions with a gait analysis system.

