##### Psychosocial well-being

The short form of the *Health Survey SF12* [48] is a questionnaire, which can be used to examine the health-related quality of life of the participants, who rate their quality of life via twelve items. The items regard eight health concepts which are commonly represented in widely used surveys: (1) physical functioning, (2) role limitations due to physical health problems, (3) bodily pain, (4) general health, (5) vitality (energy/fatigue), (6) social functioning, (7) role limitations due to emotional problems, and (8) mental health (psychological distress and psychological well-being) [49]. The SF12 physical and mental component summary scales are scored using norm-based methods. Both scales are transformed to have a mean of 50 and a standard deviation of 10 in the general U.S. population. All scores above and below 50 are above and below the average [49].

The *Satisfaction with Life Scale* SWLS [49] is a brief instrument with five items to measure global cognitive judgements of satisfaction with one’s life on a seven-point Likert scale. High scores indicate a high satisfaction with life, while low scores indicate a low degree of satisfaction.

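### Three sections of the protocol give three different primary outcome sets, and the Bonferroni correction has no stated count, so the test that decides success is not fixed

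*Protocol article*

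**What the plan says.** Three sections of the protocol article define what is primary.

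- **Primary outcomes.** The list opens with "The following primary outcomes will be measured to evaluate the efficacy of the intervention program". Under it stand SPPB, gait analysis, the Serial Sevens Test (SST), the Verbal Fluency Test (VFT), SF12 and SWLS. For the SST, "a simpler version of the SST will be administered", counting down in threes (S3T) and ones (S1T). SF12 is a "questionnaire, which can be used to examine the health-related quality of life of the participants", and "The SF12 physical and mental component summary scales are scored using norm-based methods". SWLS "is a brief instrument with five items to measure global cognitive judgements of satisfaction with one’s life on a seven-point Likert scale".
- **Statistical analysis.** "The primary analysis will be a mixed model between-group comparison of the SPPB, gait variables, Serial Sevens, and Verbal Fluency Test". SF12 and SWLS are not in this sentence. The same section says: "We will use the Bonferroni correction to appropriately adjust the overall level of significance for multiple comparisons". It gives no number of comparisons, and sets the significance level at 0.05.
- **Sample size estimate / power calculations.** The calculation is "based on the primary outcome Short Physical Performance Battery (SPPB", in the singular, with power 0.80 and a two-sided error written as a 95% confidence level, that is 0.05 without correction.

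**The concern.** The three statements cannot all hold. SF12 and SWLS are primary in one section and outside the primary analysis in another, and a third section treats SPPB as the only primary outcome. Each is stated outright, so this is a contradiction and not detail left out for brevity.

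A Bonferroni correction protects the error rate only over a family fixed in advance. If the family can be settled after the data are seen, the threshold that SPPB must meet can be settled then too. The confirmatory standing of the result is at stake in a trial meant to yield recommendations for the health care system (Discussion). The sample size is also tied to only one of the possible readings.

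**Working it through.** **1. The plan's own figure.** Inputs from the sample size section: repeated-measures ANOVA, within-between interaction, 2 groups, m = 3 measurements, small effect, power 0.80, two-sided 0.05, N = 108 per region. The section does not give the correlation ρ or the value of f.

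Method: noncentral F with λ = f²·N·m/(1−ρ), df1 = 2, df2 = 2(N−2), sphericity assumed.

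- f = 0.10 and ρ = 0.5 (both assumed): N = 164 for 80%; power at 108 is 0.61.
- 108 gives 0.80 with f = 0.10 if ρ ≈ 0.668: λ = 0.01 × 108 × 3/0.332 ≈ 9.8. It also does so with ρ = 0.5 if f ≈ 0.123.
- 108 × 1.3 = 140.4, taken as 140; 8 × 140 = 1120.

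So 108 can be obtained, but only with an unstated input. It is not shown to be wrong.

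**2. How many comparisons the text supports.**

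| Source | Primary set | k | 0.05/k |
|---|---|---|---|
| Sample size | SPPB | 1 | 0.05 |
| Statistical analysis | SPPB, gait, serial test, VFT | 4 | 0.0125 |
| Primary outcomes | the same plus SF12, SWLS | 6 | 0.0083 |

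Counting variables gives more:

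- SPPB: 1
- gait: 4 parameters × 2 speeds = 8
- S3T, S1T and VFT: 3 × (2 counts + 4 dual-task gait parameters) = 18
- sum: 27; with two SF12 scores and one SWLS score, 30 (0.05/30 = 0.00167)

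This longer count is my own reading; the protocol does not state it.

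**3. What the choice does to a result.** Take a hypothetical SPPB p-value of 0.01. It is significant at k = 1 and k = 4 (0.01 < 0.0125) but not at k = 6 (0.01 > 0.0083). A p-value of 0.02 is significant only at k = 1.

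**4. Power at the corrected level.**

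- A: one region, N = 108, f = 0.10, ρ ≈ 0.668 (chosen so that k = 1 gives 0.80).
- B: 784 pooled completers (1120 × 0.7), f = 0.10, ρ = 0, clustering ignored.
- C: one region, 54 per arm, the stated 1.0 point with SD 0.99, two-group normal approximation Φ(δ/(σ√(2/n)) − z₁₋α/₂).

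| k | A | B | C |
|---|---|---|---|
| 1 | 0.80 | 0.99 | >0.99 |
| 4 | 0.62 | 0.98 | >0.99 |
| 6 | 0.56 | 0.97 | >0.99 |
| 30 | 0.37 | 0.92 | 0.98 |

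Column A only illustrates that 0.80 belongs to k = 1. Columns B and C show that the loss does not carry over to the pooled trial at f = 0.10, or to the stated 1.0-point target. As a less favourable assumption, a pooled two-group comparison at d = 0.2 with 392 per arm and no baseline adjustment falls from 0.80 (k = 1) to 0.62 (k = 4) and 0.56 (k = 6). The protocol does not state that effect.

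**The case against.** Several primary outcomes under Bonferroni are a legitimate design, and sizing on one of them is common. The choice of gait parameter, speed or task condition is often left to an analysis plan. SF12 and SWLS are not left without analysis, because the Statistical analysis section covers every outcome. All of this stands. It does not explain why three sections name three different sets: an analysis plan would have to overrule at least one of them.

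A reader might infer four stronger points, which the document does not support:

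- **That Bonferroni contradicts the 0.05 level.** The 0.05 can be the overall level that the correction protects, and the wording on adjusting the overall level fits that. Only the sample size calculation is tied to an uncorrected level.
- **That a test in the primary analysis is never given.** Serial Sevens is most naturally a loose name for the SST, which the outcomes section says is given as S3T and S1T.
- **That the false-positive rate is that of a few dozen uncorrected tests.** The promised correction rules this out. The open risk is a denominator chosen late.
- **That the trial is underpowered.** The per-region loss rests on a correlation found by working back from 108, and pooled power for f = 0.10 stays high.

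**Conclusion.** The point holds as a contradiction within the protocol about which outcomes are primary, joined to a Bonferroni rule that cannot be applied as written. The named sets give k = 1, 4 or 6, so the level for SPPB can differ by a factor of six (0.05 against 0.0083), and by more if variables are counted one by one. The stated 0.80 power is valid only for SPPB at 0.05.

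These conclusions need only the text and division of 0.05 by k. The per-region figures (0.62 at k = 4, 0.56 at k = 6) are illustrations that assume f = 0.10 and a correlation of about 0.67. The pooled figures ignore clustering. The harm shown is an unfixed success criterion, and a trial-level loss of power is not shown.

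**What to change.** Before outcome data are seen, make the Primary outcomes, Statistical analysis and Sample size sections agree.

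- **Preferred.** Name the SPPB total score at 16 weeks, compared between groups, as the single primary outcome at two-sided 0.05. The sample size section already assumes SPPB at that level, and 16 weeks is the only follow-up in both arms, since the 32-week assessment is made in the intervention group only. Move gait, S3T/S1T, VFT, SF12 and SWLS to a counted secondary list, tested with Holm or in a fixed order.
- **Alternative.** Keep several primary outcomes. Name one variable for each, state k and whether one, some or all must be significant, and restate the power at 0.05/k.
- **Either way.** Write S3T/S1T in place of Serial Sevens, as a wording correction.

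The cost is a change of wording. With the preferred option, the small downside is that gait, cognition and quality of life lose primary status. With the alternative, the power statement must be recalculated.
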